## 3. Expected Results

Based on the reviewed bibliography, the type of design of the present study, the proposed objectives and the characteristics of the intervention that will be carried out, we hope that the results will reveal the feasibility and clinical usefulness of the UP applied in an online group format, in a mental health setting of the national health system for candidates of BS who have at least one diagnosis of ED or emotional symptoms. The concrete results that are expected to reach this conclusion are shown in more detail in Table 4.

Reporting of results will follow the Consolidated Standards of Reporting Trials (CONSORT) recommendations, specifically its extension for designs N-of-one Trials [81].

## 4. Discussion

Obesity and being overweight have become a serious public health problem due to their high prevalence and associated costs [2,9]. EDs are highly present in people with obesity [7], and this can interfere with a commitment to voluntary weight loss [82] and it is also associated with worse post-intervention outcomes [11]. An intervention based on emotion-regulation training could help those patients to achieve both aims, to lose weight before the BS to prevent surgery problems and the emergence of emotional symptoms after the BS, maintaining their emotional and physical achievements over time. In addition to the clinical implications, the results derived from this study may also have an important economic impact. Thus, health policies and the managing of this health condition in public health settings could be also influenced.

To prove this, longitudinal studies are needed and some limitations regarding the interventions (specific CBT versus transdiagnostic intervention) and the delivery formats (onsite versus online) must be considered. The use of the UP in an online group intervention format in a public mental health setting with people waiting for BS has the following benefits:It can allow clinicians to use a single treatment for those candidates who present different EDs, with comorbidity, and also with subclinical symptoms or unspecified disorders [15].In other public health systems similar to the Spanish one, where onsite specific CBT is the most common delivery format, and therapy sessions occur at long intervals (e.g., more than a month) due to waiting lists, a UP online group intervention can help to increase the frequency of sessions and reduce costs because there are more patients treated simultaneously (five to eight patients in the same group), which can facilitate better patient care.Thanks to the online format, this intervention will facilitate access to psychological interventions in those candidates who face mobility challenges due to their obesity condition [31]. This innovative approach would be in line with the goals of the World Health Organization proposed in the mental health action plan to use electronic technologies to expand the delivery of mental health care [83].The fact of receiving quarterly follow-ups up to two years after treatment allows guaranteeing the prevention of relapses and maintaining the results, especially beyond the year and a half or two years, which is the moment in which the literature recognizes that pre-BS problems tend to reappear [42].Furthermore, this advantage offered by long term relapse prevention follow-ups leads to a condition of reduced healthcare costs that are associated with the care of comorbid health problems in this type of patients [3].And finally, it is known that group therapy provides benefits to the patient that are not obtained with individual treatment, such as reducing isolation, facilitating social support, and learning from the experiences of others [33], which could improve its efficiency.

Our study also has some limitations. First, some people who are going to undergo BS will prefer individual treatment, which could be a barrier to enroll those participants in our study (e.g., abandonment or decrease in UP satisfaction and effectiveness). In this case, it could be explained to the patient that group treatment resulted in greater weight losses than individual treatment, even for those clients with a preference for individual therapy and that matching clients with their preferences for individual or group therapy did not enhance treatment outcome either in terms of weight loss or improvements in psychological functioning [84]. Furthermore, a study in a sample of people with EDs diagnosis attended to in public mental health settings in Spain found that the majority of participants preferred receiving psychological treatment in an individual format, followed by group format, and, rarely, in an online format, so it will be necessary to explain to patients the advantages and disadvantages of receiving psychotherapy through individual, group, or online format to help them to decide whether or not to participate in this study [85]. In this sense, the arguments that must be strengthened to justify a group application, in addition to those mentioned previously, are the possibility of sharing experiences, the opportunity to learn from others and receive comments and support and for the online format, convenience [85]. The second main limitation, is that, due to this being a pilot study, the results must be interpreted with caution, as further RCT studies with greater rigor will be required. In this sense, it should be noted that this kind of study is an advisable cost-effective method to preliminarily examine the efficacy, feasibility and/or implementation of recent intervention programs or applications with different samples [86].

Despite the aforementioned limitations, the present study may have different implications. At the research level, it will be the first pilot study aimed at evaluating the feasibility and clinical utility of an online group format of a transdiagnostic intervention for the treatment of ED in public settings in Spain with people waiting for BS, allowing us to increase the evidence on UP’s effectiveness, flexibility, and versatility. At a clinical level, the results of the study will reveal whether UP can improve emotional symptoms in candidates and, therefore, improve the effects of BS in the long term. This would have important implications for patients, as it could achieve much more notable improvements after the intervention, and would serve to prevent relapses that generally appear in the long term around two years after BS.

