The UP is made up of eight treatment modules, five of which are considered core modules because they are focused on training different specific emotion-regulation skills [21]. Despite that the UP is a protocolized intervention, it is also flexible and versatile, allowing clinicians to use some of the modules or to change modules’ order to personalize the UP to their patients [22]. Its main objective is to enhance emotion-regulation strategies to all people presenting emotional dysregulation problems [15]. To date, the UP has shown a significant improvement in pre-treatment symptoms and has obtained effect sizes that are at least comparable to existing specific CBT interventions, in on-site and online formats [23]. Beyond the mood or anxiety disorders per se, the UP has been applied to different health problems, such as cancer [24], HIV [25], or irritable bowel syndrome [26]. Despite the positive data on the effectiveness of the UP for the treatment of EDs in different health conditions, we have found no studies about its clinical utility to improve anxiety and depressive symptoms or EDs in patients with obesity who are waiting for BS.

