The specific objectives pursued are: to evaluate adherence to treatment and clinical improvement in the primary and secondary measures after applying the UP and to study its long term clinical usefulness until two years after the intervention. Thus, the main hypotheses proposed for this study are: (1) statistically significant differences (reliable change index; RCI) will be obtained between the scores obtained at the pre-treatment, baseline, and post-treatment on the primary and secondary measures; (2) the improvements obtained after the application of the UP will be maintained in the long term (follow-ups of up to two years); (3) participants in the pilot study will report high adherence rates and high satisfaction scores regarding the treatment delivery format and its components.

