#### 2.5.1. Primary Outcomes

Primary and secondary diagnosis according to the DSM-5 criteria will be evaluated with the International Neuropsychiatric Interview (MINI [50]). Subclinical symptoms of anxiety and depression will be evaluated through the Beck Depression Inventory-II (BDI-II [46,47]) and the Beck Anxiety Inventory (BAI [48,49]). The weight gain or loss of the participants will be evaluated through the Body Mass Index (BMI).

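### Telling only patients who prefer individual care that groups lost more weight may colour the format-satisfaction result; one neutral description for every candidate would avoid this

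*Protocol article*

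**What the plan says.** The limitations paragraph in 4. Discussion expects that some candidates will prefer individual treatment, "which could be a barrier to enroll those participants in our study (e.g., abandonment or decrease in UP satisfaction and effectiveness"). Its response is that "it could be explained to the patient that group treatment resulted in greater weight losses than individual treatment". It adds that this held even for people who preferred individual therapy, and that giving patients their preferred format improved neither weight loss nor psychological functioning. The support is a cited study.

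The paragraph then cites a preference survey in Spanish public mental health services and concludes that "it will be necessary to explain to patients the advantages and disadvantages of receiving psychotherapy through individual, group, or online format". The next sentence turns back to persuasion and introduces "the arguments that must be strengthened to justify a group application".

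The related outcomes are set elsewhere:
- Weight is a primary outcome (2.5.1): "The weight gain or loss of the participants will be evaluated through the Body Mass Index (BMI").
- BDI-II and BAI are primary self-report measures (2.5.1): "Subclinical symptoms of anxiety and depression will be evaluated through the Beck Depression Inventory-II" and the Beck Anxiety Inventory.
- Hypothesis 3 (1. Introduction) predicts "high satisfaction scores regarding the treatment delivery format and its components".
- Table 4 lists high scores on the Satisfaction with Treatment Questionnaire (STQ), including its group and online format items, as an expected feasibility result.

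**The concern.** A pilot of an online group should learn whether candidates accept that format. The Discussion offers an outcome-specific argument to the very patients who doubt it, and gives the threat to enrolment, satisfaction and effectiveness as the reason. These are things the study sets out to observe.

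Two results could be affected. First, ratings of the group and online format may partly reflect what a subset was told about groups before joining. Second, some patients who would have declined because of the format may be talked round, so the refusals that would have shown limited acceptability are lost. Both bear on whether a larger trial of this format is worth running.

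**Working it through.** The plan gives no figure on this point, so there is nothing to reproduce. The check sets the passages side by side and follows the message to each outcome.

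1. **Who hears it.** By the wording in 4. Discussion, the statement is for patients who prefer individual treatment. If a fraction *p* of those enrolled hear it and their score on some measure shifts by *e* on average, the group mean shifts by *p* × *e*. The document gives neither quantity. It says only that some candidates will prefer individual treatment.

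2. **When they hear it.** In 2.2 Procedure the order is invitation, consent, pre-treatment evaluation, notice of the assigned baseline length, baseline phase, treatment. A message given at invitation comes before the pre-treatment score.

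3. **What enters a change score.** If expectancy shifts the pre-treatment score by *e_pre* and the post-treatment score by *e_post*, the pre-post change is shifted by *e_post* − *e_pre*. Only the part that differs between the two occasions enters. This applies to BDI-II and BAI.

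4. **What enters the STQ.** Table 3 has the STQ at post-treatment and follow-ups only. With no earlier score to subtract, any shift stays in the reported level in full, as *p* × *e*. The format items also rate the very feature being promoted.

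5. **What the multiple baseline protects.** Only baseline length is randomised (8, 12 or 15 days; 2.2). The repeated baseline covers the short daily battery and BMI. Table 3 shows no baseline-phase BDI-II, BAI or STQ, so the staggered start gives the first two little protection and the STQ none. Nor is there an arm in another format to compare satisfaction with.

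6. **Ranking by exposure.** STQ format items come first (self-report, no earlier score, same topic as the message). BDI-II and BAI come next (self-report, partly protected by step 3). BMI is a physical measure and the MINI an interview, so both are less open to response bias, although weight is the subject of the statement.

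7. **Direction.** It is not fixed. Raised expectations may lift satisfaction, or lower it if disappointed. Persuasion may also bring in reluctant patients who rate the format lower or attend less, which would pull the scores down.

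8. **Consistency within the paragraph.** A balanced account of the formats and an argument that one of them wins on weight, given only to doubters, are different messages. The text contains both and does not say which governs recruitment.

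**The case against.** The strongest reply is that this is a conditional remark in a limitations paragraph. 2.2 Procedure describes an invitation by informative document plus consent papers, and 2.4 Ethics says participants learn what the treatment consists of, its duration and its phases. Neither mentions weight loss by format, and the patient-facing texts are not shown. The Discussion itself calls for balance. Participation is voluntary, and 2.2 lets anyone uncomfortable with the online group move to individual onsite care. Lack of blinding comes with the design, and the STQ is completed after twelve sessions of direct experience. All of this stands and limits the point to a remark that should not be carried into recruitment.

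Several stronger readings are tempting but not supported:
- *That a recruitment script exists.* The document shows none.
- *That patients are told their BMI will improve.* The statement reports a past comparison of formats in another study and promises nothing about this trial.
- *That the trial is uncontrolled.* Section 2 describes within-person control with randomised, staggered baselines. What is missing is a parallel or alternative-format comparator.
- *That all of any expectancy effect enters the estimate, or that its size can be stated.* The order of events rules out the first for change scores, and no figure supports the second.
- *That most of those invited would hear the message.* The preference survey concerned people with emotional disorders in public services, not bariatric candidates.
- *That the Introduction contradicts the statement.* Its sentence "we have found no studies about its clinical utility to improve anxiety and depressive symptoms or EDs in patients with obesity" who await surgery concerns the Unified Protocol. The Discussion compares group with individual format. The Introduction shows only that the weight-loss statement does not rest on this intervention in this population.

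The reply does not remove the central point. The remark looks forward to how enrolment will be handled, no other section withdraws it, and the sentence on strengthening the group arguments carries the earlier statements along with the new ones.

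**Conclusion.** The point holds in limited form. The Discussion permits a selective, outcome-related and persuasive statement to candidates who prefer individual care, and the same paragraph also calls for a balanced explanation. If used, the statement may affect expectations. The STQ format items are the most exposed, BDI-II and BAI less so, and BMI and the MINI least. It may also hide refusals that are feasibility information.

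No size or sign can be given, because the document states neither how many candidates would hear the statement nor how far it would move a score. The conclusion rests on two assumptions: that the remark would be acted on at recruitment, and that participants' ratings can respond to what they were told. It is a modest point, worth acting on because the remedy costs almost nothing and protects a result the pilot exists to produce.

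**What to change.** - Leave the weight-loss comparison and the preference-matching statement out of what candidates are told.
- Give every candidate the same neutral account of individual, group and online formats, as the Discussion's own sentence on explaining them requires. Revise the sentence on strengthening the group arguments to agree with it.
- Ask format preference (individual, group or online) once at pre-treatment.
- Report refusals because of format as a feasibility result, and report STQ format scores and attendance by stated preference.

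The cost is a revision of a few sentences, one extra pre-treatment item and a count of refusals with reasons. Uptake may fall slightly, but that would itself be a valid feasibility finding. Neutral wording will not remove expectancy, since participants know what they receive. It removes only the selective part.

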## 5. Conclusions

In sum, the present study supports the idea of the need to test new forms of psychological interventions with patients waiting for BS [12]. This would allow us to improve the previous psychopathology, and, therefore, to potentiate the effects of BS in the short and long term [2].

The UP may be a good treatment option, considering that it is directed at EDs (which are the most prevalent in people with obesity problems) [12], and that it allows addressing comorbidity, subclinical symptoms, and unspecified disorders [15].

In addition, its application through an online group format can provide extra advantages, as it allows access to treatment for people with mobility problems, something very common among candidates for BS [31], and also fosters social support among the members of the group [33].

Based on all this, the results of the development of this study may have important implications for the National Health System, which will be able to meet the psychological needs of patients with obesity problems, improving their quality of life before the intervention, and enhancing its results in the long term, which will mean a reduction in costs to the system and more specialized and multidisciplinary care for patients who are in this situation.

## Figures and Tables

**Figure 1 ijerph-17-06155-f001:**
[figure not shown]
Study flow chart. BS: Bariatric surgery.

**Table 1 ijerph-17-06155-t001:** Inclusion criteria and main contraindications for BS.

**Inclusion Criteria**
- BMI >40 or 35 with associated major comorbidities
- Age between 18 and 65 years
- Long-standing obesity (3–5 years)
- Failure in dietary attempts and treatments under control
- Absence of anesthetic contraindication and acceptable surgical risk
- Not having endocrine causes of obesity
- Understanding of the weight loss process, associated problems and the stated objective
- Commitment to adhere to the monitoring standards
**Contraindications**
Relative
- Clearly unfavorable family environment
- Personality disorder
- Psychogenic vomiting
- Hyperphagia in other psychological disorders or other eating disorders
- Mild intellectual disability
- Psychotic disorders without positive symptoms
- Any psychiatric illness that significantly hinders the good follow-up and completion of the guidelines and medical indications for this process and may worsen the patient’s state of health
Absolute
- Drug dependency
- Moderate or severe intellectual disability
- Psychotic disorder with positive symptoms
- Bulimia nervosa

**Table 2 ijerph-17-06155-t002:** Treatment content split by session.

Session Number	Content
Session 1	Setting Goals and Maintaining Motivation
Session 2	Understanding your Emotions: What is an Emotion?
Session 3	Understanding your Emotions: Following the ARC (Antecedent, Response, Consequence)
Session 4	Mindful Emotion Awareness—I
Session 5	Mindful Emotion Awareness—II
Session 6	Cognitive Flexibility—I
Session 7	Cognitive Flexibility—II
Session 8	Countering Emotional Behaviors
Session 9	Understanding and Confronting Physical Sensations
Session 10	Putting it into Practice: Emotion Exposures—I
Session 11	Putting it into Practice: Emotion Exposures—II
Session 12	Recognizing Accomplishments and Looking to the Future

**Table 3 ijerph-17-06155-t003:** Distribution of the variables administered throughout the intervention.

Measures	Pre-Treatment	Baseline	Treatment	Post-Treatment	Follow-Ups ^1^
Demographic characteristics	X				
MINI	X			X	X
BDI-II	X			X	X
BAI	X			X	X
BMI	X	X	X	X	X
PANAS	X			X	X
NEO-FFI	X			X	X
QLI	X			X	X
EuroQol	X			X	X
MI	X			X	X
DERS	X			X	X
BEAQ	X			X	X
PHLMS	X			X	X
ERQ	X			X	X
Surgical Complications	X				
BITE	X			X	X
BSQ	X			X	X
EES	X			X	X
OASIS			X		
ODSIS			X		
OESIS			X		
PESIS			X		
STQ				X	X
Baseline assessment battery ^2^		X			
Assessment battery during treatment ^3^			X		

Note: MINI: International Neuropsychiatric Interview; BDI-II: Beck Depression Inventory-II; BAI: Beck Anxiety Inventory; BMI: Body Mass Index; PANAS: Positive and Negative Affect Scale; NEO-FFI: NEO Five-Factor Inventory; QLI: Quality of Life Index; MI: Maladjustment Inventory; DERS: Difficulties in Emotion Regulation Scale; BEAQ: Brief Experiential Avoidance Questionnaire; PHLMS: Philadelphia Mindfulness Scale; ERQ: Emotion Regulation Questionnaire; BITE: Bulimic Investigatory Test; BSQ: Body Satisfaction Questionnaire; EES: Emotional Eating Scale; OASIS: Overall Anxiety Severity and Impairment Scales; ODSIS: Overall Depression Severity and Impairment Scales; OESIS: Other Emotions Severity and Impairment Scale; PESIS: Positive Emotion Severity and Impairment Scale; STQ: Satisfaction with Treatment Questionnaire. ^1^ Quarterly follow-ups up to two years after treatment; ^2^ For more information about the specific items that make up the baseline assessment battery see section “Baseline assessment”; ^3^ For more information about the specific items that make up the assessment during treatment battery see section “Assessment during treatment”.

**Table 4 ijerph-17-06155-t004:** Main expected outcomes. UP: Unified Protocol for the transdiagnostic Treatment of Eds.

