## Abstract

Obesity is currently becoming a serious global public health problem due to its high prevalence and continuous increase. This condition is associated with different physical and mental health problems. The presence of emotional disorders (anxiety, depression and related disorders) among candidates for bariatric surgery is very high and predicts worse physical and psychological results. The present study aims to explore the feasibility and clinical usefulness of the Unified Protocol, a transdiagnostic emotion regulation-based intervention, delivered in an online group format to patients with emotional disorder diagnosis or symptoms, who are waiting for bariatric surgery. We will conduct a pilot study with a repeated single-case experimental design (multiple baseline design) in a public mental health service. The sample will consist of 60 participants, who will be randomized to three baseline conditions: 8, 12 or 15 evaluation days before the intervention. Diagnostic criteria, symptomatology and body mass index are the primary outcome measures, and we will include affectivity, personality, quality of life, body image, eating behavior and surgical complications like secondary measures. An analysis of treatment satisfaction will be also performed. Assessment points will include pre-treatment, baseline, treatment, post-treatment, and follow-ups every three months until two years after post-treatment. The results obtained in this study may have important clinical, social and economic implications for public mental health.

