A random assignment will be carried out to reduce the threat of selection, and the fact of choosing three conditions is one of the established standards for this type of designs in order to reduce the threat of ambiguous temporal precedence and maturation [38]. Furthermore, the fact that all three conditions involve evaluation periods of 8, 12 and 15 days is due to the established standard of having a minimum of five data points in each phase to reduce the threat of attrition [38]. By choosing at least eight, we make sure to meet it even considering the probability that participants will forget to fill out the assessment one day. Actually, the reason for choosing those days is the temporal stability of the variables that we measured through the study.

In addition, the intervention will begin in a staggered manner with individual sessions (to reduce the threat of the history) and to reduce the threat of testing, a pre-treatment assessment will be performed prior to starting the baseline, to consider that the assessment process itself can have therapeutic effects on participants [38].

The study includes five assessment moments (pre-treatment, baseline, treatment, post-treatment, and follow-up, one every three months until two years after treatment completion). The flow chart of the study design is shown in Figure 1.

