The baseline and psychological intervention will be conducted between the period of acceptance for BS and the BS implementation, that last approximately one year in public health settings. The intervention will be carried out in an online group format through the Cisco Webex platform. The UP will be applied in twelve weekly 2-h online group sessions. To comply with the experimental design of the multiple baseline, when each participant completes the baseline evaluation, they will receive the first online session in individual format (to receive the first session in stages), then they will continue with the second session and the rest of the treatment in group format. The content of each session is shown in Table 2. Participants will receive the therapy support manual [11]. The online group will consist of five to eight participants, one therapist ([name]), and one co-therapist ([name]). For ethical reasons, if any of the patients feel uncomfortable during the study with the online group format, they may leave the group and receive individual onsite attention (treatment as usual). In this case, the content and estimated number of sessions will be the same, although the frequency will be stipulated by the mental health unit depending on its possibilities.

The study plans to conduct a follow-up assessment every three months until two years after treatment completion. All follow-ups will be conducted online. Considering the time interval of the baseline, the psychological intervention and the BS procedure, the two first follow-ups (three and six months after intervention) will be conducted before BS, and the rest will be conducted after BS. In addition, at the baseline and during treatment, the participants must fill out an online survey made up of 14 questions that will ask about the intensity of the emotions of happiness, sadness, anxiety, other emotions, difficulties in emotion regulation, body image, and emotional eating. Through this weekly evaluation, we expect to observe how the participants evolve in the different variables throughout the different treatment modules.

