#### 2.5.2. Secondary Outcomes

Secondary outcomes can be grouped around: affectivity, personality traits, quality of life and interference, emotion regulation, aspects related to surgical complications, eating behaviors and body image, and satisfaction with and evaluation of the treatment received.

To assess affectivity, the Positive and Negative Affect Scale (PANAS [53,54]) will be administered to evaluate positive and negative affect. Personality will be measured with the NEO Five-Factor Inventory (NEO-FFI [55]), which offers a rapid and general measure of the Big Five personality traits of which we will only assess Neuroticism and Extraversion. The Quality of Life Index (QLI [56]) will be used to evaluate several aspects related to quality of life (i.e., physical disability, emotional well-being, self-care and independent functioning, occupational functioning, interpersonal functioning, social–emotional support, community and services support, personal fulfillment, spiritual fulfillment, and overall quality of life). EuroQol [57,58] is a generic instrument that will be used to measure health-related quality of life. It has five dimensions (mobility, personal care, daily activities, pain, and anxiety/depression), and a general state of health perceived through a visual analog scale. Similarly, the Maladjustment Inventory (MI [59]) will be used to evaluate the extent to which the subject’s current problems impact negatively on different areas of daily life, namely, work, social life, leisure time, relationship with the partner, family life, and overall adjustment in daily activities.

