Regarding emotion regulation, it will be assessed using the Difficulties in Emotion Regulation Scale (DERS [60,61]), which presents five dysregulation dimensions: emotional lack of control, emotional rejection, life interference, lack of emotional attention, and emotional confusion. In addition, to assess the different emotion regulation skills that will be trained through the UP, we will use the Brief Experiential Avoidance Questionnaire (BEAQ [62,63]), which is a self-report questionnaire with 15 items that measure experiential avoidance; the Philadelphia Mindfulness Scale (PHLMS [64,65]), which is a 20-item questionnaire that assesses two mindfulness constructs: awareness and acceptance and the Emotion Regulation Questionnaire (ERQ [66,67]), which is a self-report questionnaire commonly used to assess two emotion-regulation strategies: cognitive reappraisal (six items) and expressive suppression (four items).

To assess surgical complications, the professional will be asked to refer the participant to the mental health unit a report describing the course of the operation and the recovery from it. Specific measures related to eating disorders will also be used, such as the Bulimic Investigatory Test (BITE [68,69]), which is a self-report questionnaire used to evaluate the presence and severity of bulimic symptomatology, and cognitive and emotional signs and symptoms associated with binge eating; the Body Satisfaction Questionnaire (BSQ [70,71]), which is a self-applied scale used to evaluate the fear of gaining weight, feelings of low self-esteem because of one’s appearance, the desire to lose weight, and body dissatisfaction, and Emotional Eating Scale (EES [72]), which is a 25-item self-report assessing a person’s tendency to cope with negative affect through eating. Participants’ weight will be checked monthly to calculate their body mass index (BMI).

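### Table 3 schedules the secondary outcome of surgical complications at pre-treatment only, months before any operation, so as scheduled it cannot be observed

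*Protocol article*

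**What the plan says.** The abstract lists "body image, eating behavior and surgical complications like secondary measures", and section 2.5.2 repeats this, naming "aspects related to surgical complications, eating behaviors and body image, and satisfaction with and evaluation of the treatment received" among the secondary outcome groups. The same section says how complications are to be measured: a professional is asked to send the mental health unit "a report describing the course of the operation and the recovery from it". It does not say when.

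Table 3 is the article's only measure-by-measure schedule. Its row "Surgical Complications" carries a single X, under Pre-Treatment. Baseline, Treatment, Post-Treatment and Follow-Ups are empty, and the notes to the table add nothing about the row.

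On timing, section 2 states that "a pre-treatment assessment will be performed prior to starting the baseline". Section 2.2 states: "The baseline and psychological intervention will be conducted between the period of acceptance for BS and the BS implementation, that last approximately one year". It adds that "the two first follow-ups (three and six months after intervention) will be conducted before BS, and the rest will be conducted after BS".

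**The concern.** A report on an operation and the recovery from it cannot be obtained at a visit held before the operation. Table 3 nevertheless gives that visit as the only collection point and leaves the follow-up column blank, although most follow-ups fall after surgery.

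This is a named secondary outcome, and it bears directly on the suggestion in the Discussion that the intervention could help to prevent problems with surgery. A data-collection form built from Table 3 would ask for the report when none can exist and would not ask for it later, so the field would be empty or meaningless for every participant. The report also comes from another professional and not from the participant's online survey, so obtaining it depends on a request made at the right time.

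**Working it through.** The plan states no figure to reproduce here. The check sets the table row against the text and counts days on the protocol's own intervals.

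**1. Order of events**

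| Step | Source |
|---|---|
| Pre-treatment assessment, before baseline | Section 2 |
| Baseline of 8, 12 or 15 days | Sections 2 and 2.2 |
| Treatment: "The UP will be applied in twelve weekly 2-h online group sessions" | Section 2.2 |
| Post-treatment, then follow-ups at 3 and 6 months, all before surgery | Section 2.2 |
| Surgery, about one year after acceptance | Section 2.2 |
| Remaining quarterly follow-ups to two years, after surgery | Section 2.2 |

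**2. Day count from the start of baseline**

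- Treatment: 12 × 7 = 84 days.
- Post-treatment: 8 + 84 = day 92 to 15 + 84 = day 99.
- 6-month follow-up (about 182 days later): 92 + 182 = day 274 to 99 + 182 = day 281.
- 9-month follow-up (about 274 days after treatment): 92 + 274 = day 366 to 99 + 274 = day 373.

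If baseline starts soon after acceptance, surgery at about one year (day 365) falls between the 6- and 9-month follow-ups, as section 2.2 says. The pre-treatment visit precedes day 0. It is therefore at least about 274 days, roughly nine months, before surgery, and nearer one year if the stated waiting time holds.

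**3. Visits that could capture the outcome**

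Quarterly follow-up for 24 months gives 24 / 3 = 8 visits. Two precede surgery, which leaves 8 − 2 = 6 after it, the first at 9 months. Table 3 marks none of the eight for surgical complications.

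**4. Could the mark be right for another reason?**

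- *Column shift in the text extraction.* Unlikely. Nearby rows keep their empty cells: OASIS is marked under Treatment, and STQ under Post-Treatment and Follow-Ups. The row has the same layout as demographic characteristics, which is properly pre-treatment only.
- *A pre-operative meaning.* The article describes no pre-operative risk rating and no history of earlier operations under this label.
- *General statement in section 2.5.* That section says primary and secondary outcomes are assessed before treatment, after it and at follow-up, then refers the reader to Table 3 for the distribution. The other 17 outcome measures in sections 2.5.1 and 2.5.2 are all marked at both Post-Treatment and Follow-Ups. Surgical complications is the only exception.

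**The case against.** The strongest reply is that the text already plans the collection. Section 2.5.2 calls for a report triggered by the surgery itself, not a questionnaire tied to a visit, and staff following that section could obtain it only after the operation. On this view the X is a misplaced mark, no data-collection form is shown, and actual loss of the outcome is not demonstrated. Nothing primary depends on the row: the repeated-measures tests in section 2.6 do not suit a one-off narrative report, and Table 4 gives no expected direction for complications. Finally, marking several follow-ups could turn one report into a repeated quarterly measure that the article does not describe.

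Part of this stands. The outcome is measurable in principle, the mark is probably clerical, and the primary outcomes, sample size and randomization are untouched. Whether staff would follow the table or the text is unknown. The caution about repeated measurement is fair and is met in the wording of the fix.

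The rest does not remove the problem. Section 2.5.2 gives no collection time that could override the table, and the general sentence in section 2.5 sends the reader to that table. Table 4 also gives no explicit direction for BMI, a primary outcome, so absence from it says little about importance. Nor is this a detail left to a fuller document: the article states a time point, and that time point is incompatible with its own text.

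**Conclusion.** The concern holds. As scheduled in Table 3, surgical complications cannot be observed: the single marked visit is at least about nine months before surgery, and none of the six post-surgery follow-ups is marked. Under the table, all post-operative complication data are unscheduled.

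This rests on reading the row as printed, on section 2.2's placement of surgery after the 6-month follow-up, and on taking twelve weekly sessions as 84 days. Moderate changes in the actual waiting time would not alter it, because the pre-treatment visit precedes surgery in every case. The defect concerns one secondary outcome and should be corrected before the table is used to build forms or to judge the completeness of reporting.

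**What to change.** - In Table 3, remove the pre-treatment mark for surgical complications and mark the follow-ups after surgery. A footnote should say that these are the visits at which the single surgical report is requested or confirmed as received, so that the mark is not read as a new quarterly measure.
- Record each participant's surgery date and tie the request for the report to it. The actual date will vary around the approximate one-year wait, so a fixed visit number alone may miss some operations.
- Report complications among participants who were operated on, and give that number as the denominator.
- Make section 2.5.2 and the general sentence in section 2.5 agree with the corrected row.

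The cost is one table row, one footnote and one date field on the form. The report itself is already planned, and nothing in patient care changes.
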